### Ethical considerations and dissemination

Data will be handled confidentially and reporting will be coded. Each participant is given a personal code, which can only be linked to a person when the coding key is known. Collected data and personal information will be stored separately. The coded dataset will be available to the research team, healthcare inspectorate, study monitors, and members of the medical research ethics committee. The handling of personal data will comply with the General Data Protection Rule and the Research Data Management Code of Conduct of Maastricht University. Data will be used for future studies if the patient agreed upon this in the informed consent form. Data and material will be stored for 15 years in a repository of Maastricht University and can be made available to researchers upon request.

Participants will be compensated for any harm or injury due to participation in the study. The sponsor/investigator has liability insurance, which is in accordance with article 7 of the Medical Research involving Human Subjects Act. All adverse events will be followed until they have abated, or until a stable situation has been reached. Depending on the event, follow up may require additional tests or medical procedures as indicated, and/or referral to the general physician or a medical specialist. Any further treatment required for mood complaints after termination of the intervention will be arranged within the healthcare system. Adverse events will not be reported in the publication unless an adverse event occurs often and will, therefore, lead to a bias.

Ethics approval for the study has been given by the medical research ethics committee of Maastricht University Medical Centre and Maastricht University (committee reference number NL65349.068.18). Any protocol modifications will be communicated to the ethics committee. The study will be monitored by the Clinical Trial Centre Maastricht. In every site, there will be a site initiation visit, two monitoring visits, and a close-out visit. The monitoring will be performed independently of investigators and the sponsor.

In accordance with the Central Committee on Research Involving Human Subjects statement on publication policy, the researchers aim to publish the results of the study (positive or negative) in international, peer-reviewed journals. Furthermore, results will be presented at professional conferences and provided to study participants upon request. The standard protocol items: recommendation for interventional trials (SPIRIT) checklist for this trial is shown in Additional file 1.

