### Procedure

Participants will be recruited at participating hospitals and rehabilitation centers in the Netherlands. To prevent unnecessary burden, the psychologists will check the inclusion and exclusion criteria. If the patient is willing to participate the investigator will meet with the patient (at the patient’s home, the hospital, or the university, as preferred by the patient) to discuss the participation in the study and answer questions. If all is clear the informed consent form will be signed by the patient and the researcher (see Additional file 2). Subsequently, the first measurements will take place (T0) and the participant will be randomly allocated to the experimental group receiving ACT or to the active control group receiving psycho-education. The therapy sessions will be scheduled with the psychologist or healthcare professional. One month after the start of the intervention both groups will fill in the questionnaires for T1 (see Fig. 2). Questionnaires will be filled in on paper and measurements will be conducted by a research assistant blinded to allocation. After 3 months, when the treatment program is completed, the participants will fill in the questionnaires for T2. There will be follow-up measurements at 7 months (T3) and 12 months (T4). Again, these measurements will be conducted by a research assistant blinded to allocation. Research assistants will enter the data and data entry will be periodically checked during the monitoring visits. Follow-up appointments will be planned at the end of each visit. The research assistant will remind participants of their appointment by telephone or e-mail 1 week before the appointment is due. During the assessments, the researcher and research assistants will be alert for any adverse events such as suicidality. All adverse events related to mood complaints reported spontaneously by the subject or observed will be systematically collected and reported to the medical research ethics committee. Based upon these events the decision may be made to discontinue participation in the study. Furthermore, participants can leave the study without any consequences, at any time, for any reason if they wish to do so. The investigator can decide to withdraw a subject from the study for urgent medical reasons.

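### The publication rule leaves out adverse events unless they occur often, so individual events such as suicidality could go unpublished in either arm

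*Protocol article*

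**What the plan says.** Three statements in the protocol article bear on this.

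- **Publication.** Ethical considerations and dissemination: "Adverse events will not be reported in the publication unless an adverse event occurs often and will, therefore, lead to a bias". The same section says of publication in general that "the researchers aim to publish the results of the study (positive or negative) in international, peer-reviewed journals".
- **Collection.** Procedure: at assessments "the researcher and research assistants will be alert for any adverse events such as suicidality", and "All adverse events related to mood complaints reported spontaneously by the subject or observed will be systematically collected". These are passed to the medical research ethics committee. The section adds: "Based upon these events the decision may be made to discontinue participation in the study".
- **Follow-up.** Ethical considerations and dissemination: "All adverse events will be followed until they have abated, or until a stable situation has been reached".

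Neither section says how many events count as frequent, whether they are counted per arm or overall, how a bias would be recognised, or whether serious events are treated differently.

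**The concern.** The rule selects on frequency and a presumed bias. Seriousness and treatment arm play no part in it. Participants enter with raised HADS depression or anxiety scores, and the event that the article itself singles out is suicidality. In a trial of 94 people such an event would be expected in small numbers, if at all, and small numbers are what a frequency filter removes.

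The terms are also open. Whether an event type is frequent enough can be settled only after the events have been counted, so the content of the harms report depends on the results.

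The rationale is misplaced too. Harms are reported so that readers can set them against benefit, whether or not they distort the efficacy estimate. The Discussion foresees use in clinical practice if the intervention is effective. A paper silent on adverse events under this rule could not be told apart from one in which none occurred.

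**Working it through.** **The text.** Set side by side, the Procedure section creates a record of mood-related events, and the publication sentence keeps that record out of the paper unless its condition is met. The general promise to publish positive or negative results does not mention adverse events, so it does not clearly override the specific sentence about them. This is a positive statement of what will be withheld, so it is not a detail left to a fuller document.

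**Inputs for an illustration.**

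- 94 recruited, 15% drop-out expected, at least 80 required (Sample size calculation).
- 1:1 allocation (Randomization and blinding), nominally 94 / 2 = 47 per arm.
- After drop-out: 47 × 0.85 = 39.95, about 40 per arm, which agrees with 80 / 2 = 40.
- Event risk: **the article gives none.** Values of 1%, 2% and 5% are assumed to show a range.

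The plan has no adverse-event figure to reproduce. These numbers only show what counts a trial of this size might produce.

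**Chance of at least one event in an arm.** With independent patients and risk p, this is 1 − (1 − p)^47, and the expected count is 47p.

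| Assumed risk | Expected count, 47 patients | Chance of at least one, 47 patients | Chance of at least one, 94 patients |
|---|---|---|---|
| 1% | 0.47 | 1 − 0.99^47 = 38% | 61% |
| 2% | 0.94 | 1 − 0.98^47 = 61% | 85% |
| 5% | 2.35 | 1 − 0.95^47 = 91% | 99% |

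The last column uses the same formula with exponent 94 and the same risk in both arms. Over this range some events are quite likely to occur, at an expected count between about half an event and a little over two per arm.

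**What zero events would mean.** The one-sided 95% upper bound on the risk after no events in n patients is 1 − 0.05^(1/n).

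- n = 47: 1 − 0.05^(1/47) = 6.2%.
- n = 40: 1 − 0.05^(1/40) = 7.2%.

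Both bounds assume that every event among the n patients is detected. Collection relies on spontaneous report or observation, so the real uncertainty is larger.

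**Imbalance at low counts.** With 47 per arm, a split of 5 against 0 gives a two-sided Fisher exact p of 0.056, and 6 against 0 gives 0.026. Noticeable imbalances can thus arise from a handful of events, and a significance test is no substitute for printing the counts.

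**The case against.** The strongest reply is that participants are protected without publication. Mood-related events go to the ethics committee, all events are followed until resolved or stable, the inspectorate and monitors can see the coded data, and researchers may request the data. The rule touches neither allocation nor outcome measurement, the primary estimate or the sample size, and the authors can put it right when writing up. All of this stands, and it limits the point to published reporting. It does not answer the point, because readers of the paper see none of those channels.

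A reader might infer more than the article supports:

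- **That worsening could go unseen.** Symptom change on the HADS and DASS-21 is the primary outcome, and the Statistical analysis section plans baseline-adjusted mean differences with 95% confidence intervals at each time point. Mean worsening of one arm relative to the other would appear. Only individual events or individual deterioration could be missed.
- **That a rare event could never qualify for publication.** This cannot be shown, because the threshold is undefined. An expected count of 0.94 is an average, not a ceiling, and the 2% behind it is an assumption. Low counts would probably be excluded; no more can be said.
- **That publishing the collected events would give a full account of harms.** The article commits to systematic collection only for mood-related events, reported spontaneously or observed.
- **That the upper bounds measure the damage done by the rule.** They describe what a trial of this size can exclude. They show only why silence should not be read as safety.

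**Conclusion.** The point holds in its limited form. Followed as written, the sentence lets individual mood-related adverse events, including suicidality, occur in either arm and stay out of the publication, under a criterion that is undefined, is applied after the events are counted, and makes no exception for seriousness. Neither the promise to publish positive or negative results nor the availability of data on request lifts it.

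The size can only be illustrated: a 38% to 91% chance of at least one event per arm for assumed risks of 1% to 5%, and an upper bound of 6.2% to 7.2% after zero events. These rest on nominal arms of 47 (or 40 after drop-out), independent patients and, for the bounds, complete detection. The textual finding depends on none of them. It casts no doubt on safety monitoring, the primary analysis or the sample size.

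**What to change.** Replace the sentence with a commitment along these lines: all adverse events collected in the trial, including suicidality and discontinuations because of such events, will be reported by arm in the main publication, as numbers of patients and of events, whatever their frequency. State next to it that systematic collection covers mood-related events reported spontaneously or observed, so that readers know what the counts can and cannot show.

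Optionally, report by arm the number of patients with reliable deterioration beside the number improved, using the reliable change index that the Statistical analysis section already plans. This would be an addition; the plan is not contradictory without it.

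The cost is one sentence in the protocol and one table in the paper, from data that the trial already undertakes to collect. The sample size and the conduct of the trial do not change.

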## Discussion

Currently, there are no evidence-based treatment options for people with ABI who experience psychological distress. To our knowledge, no large RCTs have been conducted investigating the effectiveness of ACT for anxiety and depressive symptoms following TBI or stroke. However, earlier studies have shown promising results [29–31]. The aim of the proposed study is to investigate the clinical and cost effectiveness of an upcoming cognitive behavioural therapy, ACT, for anxiety and depressive symptoms following ABI.

We have taken into account recommendations made by Ost [18], to enhance the quality of studies in the field of ACT, such as having an active control intervention, timing of follow-up measurements, and choice of outcome measures. As described earlier, the aim of ACT is to change the functions and context of behaviour and thoughts; symptom reduction is not a treatment outcome [21]. However, the primary outcome measures in this study are the HADS and DASS-21 (measures of anxiety and depression). We have chosen these outcome measures for several reasons. First, a reduction in symptomatology (such as a decrease in psychological distress) is still regarded as a beneficial treatment outcome in ACT next to an increase in psychological flexibility. Second, when psychological flexibility increases, a decrease is often observed in psychological distress [22, 23]. We expect that a decrease in anxiety and depression is elicited through an increase in psychological flexibility. Psychological flexibility is measured with the secondary process outcomes. Last, choosing the HADS and DASS-21 as primary outcome measures will aid comparability with studies outside the field of ACT.

This study has several strengths. First, it has a relatively large sample size. Second, the study has a long follow-up period. Third, the ACT intervention will be compared to an active control intervention that has been shown to have positive effects on anxiety and depressive symptoms following brain injury. Fourth, the ACT treatment protocol was adapted to the needs and possible cognitive deficits of patients with brain injury. These adaptations were based on suggestions made in previous literature and knowledge gained in clinical practice. Fifth, the effectiveness of the ACT intervention will be investigated in a quantitative as well as qualitative manner.

This study also has certain limitations. First, its clinical nature prevents blinding of the participants and the therapists. However, the assessments will be performed by research assistants unaware of group allocation. Second, participant recruitment and loss to follow up are known to be problematic in studies with patients with ABI. To aid study adherence research assistants will be trained and the outcome assessments will take place at the participants’ home, the University, or the hospital, as preferred by the participant.

The results of this study notwithstanding should contribute to the limited knowledge on how to treat psychological distress following ABI. If effective, the BrainACT intervention can be implemented in clinical practice. Given the high prevalence of anxiety and depressive symptoms, it has the potential to help a large number of patients with ABI.

### Trial status

Recruitment started on 24 April 2019 and is expected to be completed by 1 May 2021. Protocol version 8.0, date 21 October 2019.

## Data Availability

Not applicable.

## Abbreviations

AAQ-ABI: Acceptance and Action Questionnaire after brain injury
AAQ-II: Acceptance and Action Questionnaire II
ABI: Acquired brain injury
ACT: Acceptance and commitment therapy
CFQ-7: Cognitive Fusion Questionnaire
DASS-21: Depression Anxiety Stress Scale
EQ-5D-5 L: Five-dimensional five-level EuroQol
HADS: Hospital Anxiety and Depression Scale
RCT: Randomized controlled trial
SF-12: Short Form Survey
TBI: Traumatic brain injury
USER-P: Utrecht Scale for Evaluation of Rehabilitation-Participation
VLQ: Valued Living Questionnaire
